### 9.2.2 Safety outcomes

Primary laboratory safety endpoints include serum creatinine and phosphorus for kidney function, and AST and ALT for hepatic function. Here, laboratory safety events for creatinine are defined as the occurrence of grade 2-4 serum elevations at any time during follow-up. Laboratory safety events for phosphorus, AST, and ALT are defined as the occurrence of grade 3-4 laboratory abnormalities during follow-up. Twelve-month cumulative event probabilities for each of these endpoints will be estimated based on the time to the first event using the Kaplan-Meier method and Greenwood's formula for standard errors. Differences in the estimated 12-month event probabilities between treatment groups will be presented along with 95%

confidence intervals. In addition, changes in lab results between baseline and follow-up visits will be summarized descriptively (e.g., tabulating means, medians, standard deviations, ranges, and number of participants with abnormal values), by treatment group and site.

The frequency and percentage of adverse events will be tabulated by body system. Listings of all AE's will include information on duration, outcome, severity, and relation to product use. Differences between treatment groups in the frequency of body-system level AE's will be evaluated using exact, two-sided 0.05 level tests, and approximate 95% CIs stratified by site.

### **9.3 Interim Analysis Plan Summary**

FHI will conduct interim analyses of safety data at 6 and 12 months after enrollment begins (see section 10.3). Each interim analysis will include comparability of masked treatment groups at enrollment, compliance with intervention, discontinuation rates, and intervention-associated morbidity.

In addition to providing safety data summaries, a biostatistician not otherwise associated with the study will perform an interim study size re-assessment calculation prior to the first interim safety analysis. S/he will make recommendations to the DMC regarding the potential need to increase study size if HIV infection or follow-up rates are lower than anticipated (a reduction in the total study size on grounds of excess power will not be permitted). Any such recommendations will be based on the infection rate pooled across both treatment groups, and not on observed differences between treatment groups; hence, no type I error rate adjustment will be required when evaluating the primary hypothesis test specified in section 9.2.1.

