#### ***3.3.4 Decoding procedure***

The FHI Randomization Manager will keep the randomization code. The Manager will provide the code to the FHI Study Clinician if needed to reveal the masking to the Investigator for emergencies. The Manager will provide the code to the DMC during meetings to review the interim data. The Manager will provide the code to the statisticians when they are prepared to unmask the code after completion of the final masked analysis of the data.

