## 9.2 Analysis Plan Summary

A detailed analysis plan that covers both the final analysis and the planned interim analyses will be developed and approved prior to initiation of the study. The following is a summary of the planned analyses. Any deviations to be made from this summary plan will be documented in the detailed analysis plan.

All primary and most secondary analyses will be conducted on an intent-to-treat basis. However, in order to assess the effectiveness and safety of TDF among those participants who complied with key aspects of the study protocol and to evaluate the potential impact of treatment on loss to follow-up, various additional analysis populations may be defined in the detailed analysis plan. Any key decisions regarding the timing of outcomes, the appropriateness of test statistics or model assumptions, or any other statistical issues will be made in a masked review of the data (i.e., masked to the true treatment assignments). Unmasking with respect treatment assignment will only be done for the final interpretation of the results, unless otherwise required by the data monitoring committee (DMC) (see section 10.3).

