## **10.3 Data Monitoring Committee**

A Data Monitoring Committee (DMC) will review the safety profile of this study while the study is ongoing. The committee will convene 6 and 12 months after start of enrollment. The DMC will examine the safety results of the trial. The results broken out by the treatment groups will remain masked for the FHI personnel.

No formal stopping rules will be used by the DMC for safety outcomes. Rather, a clinical assessment will be made to determine if the nature, frequency, and severity of adverse effects associated with TDF warrant the early termination of the study in the best interests of the participants.

FHI has no a priori intent to consider early termination of the study based on effectiveness so that the extended safety data can be collected. Data on safe use in non-HIV infected people for at least one year is as important as the HIV outcome.

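### The planned interim reports and the DMC's remit cover safety only, so an excess of HIV infections on TDF is not planned to be looked at before the end of the trial

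*Protocol*

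**What the plan says.** Section 9.3 describes both interims as safety analyses: "FHI will conduct interim analyses of safety data at 6 and 12 months after enrollment begins". It then lists their contents: "Each interim analysis will include comparability of masked treatment groups at enrollment, compliance with intervention, discontinuation rates, and intervention-associated morbidity". The only interim use of HIV data that it states is the study-size re-assessment, done before the first safety interim. The resulting recommendation to the DMC is to be "based on the infection rate pooled across both treatment groups, and not on observed differences between treatment groups".

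Section 10.3 sets the committee's task: "The DMC will examine the safety results of the trial". On stopping it says "No formal stopping rules will be used by the DMC for safety outcomes" and leaves early termination for adverse effects to clinical assessment. It adds "FHI has no a priori intent to consider early termination of the study based on effectiveness", and gives as the reason that extended safety data should be collected.

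On access, section 3.3.4 says "The Manager will provide the code to the DMC during meetings to review the interim data". Section 9.2 allows unmasking before final interpretation if the DMC requires it.

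**The concern.** In this protocol the word safety does not take in HIV infection. Section 3.1 makes HIV conversion the effectiveness endpoint and names creatinine, phosphorus, AST, ALT and adverse events as safety. Sections 9.2.1 and 9.2.2 keep that split, and section 10.3 itself sets one-year safety data beside the HIV outcome as two different things. A statistician who built the DMC report from sections 9.3 and 10.3 would leave out infections by arm.

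The reason given in section 10.3 explains why the trial would not stop early for success. It gives no reason for leaving an unfavourable difference unexamined. The participants are uninfected women in good health, and section 1.1 says that the safety profile in uninfected persons is not established. An excess on TDF of the outcome the product is meant to prevent would be the most serious harm this trial could show. The one body that sees results by arm meets twice, and neither report is planned to contain it.

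**Working it through.** **1. The plan's own figure.** Section 9.1.1 requires 30 infections for 90% power, one-sided alpha 0.05, null rate ratio 0.5 and true rate ratio 0.17. With 1:1 allocation, Schoenfeld's formula gives

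d = (1.645 + 1.282)² / (0.25 × [ln(0.17/0.5)]²) = 8.56 / (0.25 × 1.164) = 29.4, rounded up to 30.

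The stated figure reproduces.

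**2. Inputs for the interim counts.**
- From the protocol: 600 women per arm, about 6 months of recruitment and 12 months of follow-up each (section 3.2); placebo incidence 5/100 person-years and 80% follow-up at 12 months (section 9.1.1); DMC meetings 6 and 12 months after enrollment starts (section 10.3).
- Assumed here: uniform accrual; exponential loss with hazard h = −ln 0.8 = 0.223 per year; harm ratios of 1.5, 2 and 3. The ratios are illustrative and have no source in the protocol.

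**3. Expected infections.** A woman with infection hazard λ and follow-up T is expected to contribute λ/(λ+h) × [1 − exp(−(λ+h)T)] infections. At T = 1, 600 women on placebo give 26.3 and 600 on TDF at ratio 0.17 give 4.6, in total 30.8, which agrees with the plan's 30. Averaged over entry times, with infected women leaving the risk set:

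| | Month 6 | Month 12 | End |
|---|---|---|---|
| Person-years per arm, before removing infected women | 145 | 413 | 538 |
| Placebo infections | 7.2 | 20.3 | 26.3 |
| TDF infections, ratio 1.5 | 10.7 | 30.1 | 38.9 |
| TDF infections, ratio 2 | 14.2 | 39.8 | 51.3 |
| TDF infections, ratio 3 | 21.2 | 58.6 | 75.1 |

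**4. Chance that a by-arm table shows the excess.** Given n infections in total, take the smallest r with P(Bin(n, 0.5) ≥ r) ≤ 0.025. Then average P(Bin(n, μT/(μT+μP)) ≥ r) over n ~ Poisson(μT+μP), where μT and μP are the expected counts on TDF and placebo.

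| True ratio | Month 6 | Month 12 | End |
|---|---|---|---|
| 1.5 | 9% | 24% | 31% |
| 2 | 26% | 68% | 79% |
| 3 | 70% | 99% | >99% |

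If infected women are kept in the risk set (20.7 against 41.3 infections at month 12 for a doubling), the month-12 figures are 72% at ratio 2 and 26% at ratio 1.5, and the month-6 figure at ratio 2 is 27%. Hence about 70% and 25% at month 12, and about 26% at month 6. Delay until antibodies appear and delay in data entry are ignored; both would lower the interim figures somewhat.

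**5. What would still lie ahead.** At a doubling, the excess is 51.3 − 26.3 = 25.0 infections at the end, 39.8 − 20.3 = 19.5 at month 12 and 14.2 − 7.2 = 7.0 at month 6. So 5.5 excess infections fall after month 12 and 18.0 after month 6.

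**6. Type I error.** Section 9.2.1 claims effectiveness if the upper 95% bound for the rate ratio is below 0.5. A look that can end the trial only for harm removes some routes to that claim and adds none. Section 9.3 rests its own statement that no adjustment is needed on the size recommendation using the pooled rate. That stays true only if the recommendation is settled before the DMC sees counts by arm.

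**The case against.** A reader might infer that an excess on TDF could not come to light before the trial ends. The documents do not support that. The list in section 9.3 is not worded as exclusive, section 3.3.4 gives the DMC the code, and section 9.2 lets it require unmasking. Becoming HIV positive is a listed reason for product interruption (section 3.6.1), so conversions may appear indirectly in the discontinuation rates. These routes stand, but they depend on someone asking. Nothing planned would prompt the question, and section 9.3 does not say that discontinuations are reported by cause.

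A second objection is that section 9.2 promises a detailed analysis plan covering the interims, which is not shown and may contain the table. That is possible. The safety-only remit and the benefit-only reason, however, are stated in this protocol and not left to that plan.

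Third, the trial is masked and both arms receive the same condom counseling. Relaxed condom use should therefore affect both arms alike unless masking fails, and time off product pulls the ratio toward 1. This is fair: the protocol gives no ground to expect a doubling, and the ratios above only show what the table could detect.

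Fourth, the preventable number is modest. At a doubling only 5.5 excess infections remain after month 12, so even if exposure ended that day and detection were 70%, about 4 would be averted (0.70 × 5.5). At month 6 more lies ahead, but the chance of seeing a moderate excess is small. This limits the size of the point without removing it.

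Last, giving the same committee by-arm counts near the size re-assessment could undermine the pooled-rate argument in section 9.3. That objection is right, and the fix has to deal with it.

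**Conclusion.** The concern holds as a gap in planning. Followed as written, sections 9.3 and 10.3 give the DMC no by-arm comparison of HIV infections at either meeting, and the stated reason for not acting on effectiveness does not extend to harm. Under the assumptions above, the missing table would show a doubling of risk with probability about 70% at month 12 and about 26% at month 6, and a ratio of 1.5 with about 25% and 9%. As a means of detection it is therefore worth most at month 12. The safety-only remit is a deliberate design choice and contradicts nothing else in the protocol, so this is a cheap improvement and not an error that threatens the primary analysis.

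**What to change.** In sections 9.3 and 10.3:
- Add HIV infections and person-years by coded arm to the closed DMC report at both existing meetings, for review in the harm direction only. Any guideline for that review can sit in the DMC charter.
- Keep the statement that early termination for effectiveness is not intended.
- State that the study-size recommendation is fixed from the pooled infection rate before the DMC sees any HIV counts by arm, and that for this reason no alpha adjustment is needed.

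The cost is one table in two reports that are already planned and a few sentences of text. The data come from the monthly HIV tests, and the DMC already receives the code. The downside is that DMC members will see interim effectiveness data, so the order of the size recommendation and the by-arm table has to be kept and documented.

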## **10.0 MONITORING PLAN SUMMARIES**

### **10.1 Clinical Monitoring Plan**

Site visits by the FHI clinical monitors will be made in accordance with FHI policy and SOPs. The purpose of the monitoring is to assure the quality and accuracy of data collected on the DCF and entered in the database, and to determine that all regulatory requirements surrounding clinical trials are met.

The Investigator will allow the clinical monitors, the regulatory agencies, and FHI designated persons to inspect study documents (e.g., consent forms, drug distribution forms, DCF) and pertinent clinic records for confirmation of the study data.

Various authorized individuals may visit the study site to audit the progress of this study (e.g., FHI personnel, product manufacturer personnel, regulatory personnel). A site visit log will be maintained at the study site in which all site visits made by authorized individuals are recorded. All clinical records and the DCF for the participants enrolled in this study will be made available for review by these authorized individuals.

Before the study begins, the clinical monitors will conduct an evaluation visit at each site to determine the suitability of the site for the research study. In addition, there will be a study

initiation visit (study start-up), quarterly monitoring visits (to track study progress) and a close-out visit. The overall responsibility of the monitors is to ensure that the study is being conducted according to the protocol, FHI SOPs, ICH/GCP and applicable regulatory requirements.

A detailed monitoring plan will be developed for this study and will be used by all clinical monitors. This plan will specify the responsibilities and qualifications of the identified clinical monitors, back-up provisions, in-house monitoring procedures, and site monitoring visit procedures. All monitoring visits will be documented.

## **10.2 Safety Monitoring Plan**

The Study Clinician will review all abnormal safety parameter AEs (creatinine, phosphorus, ALT, or AST). The Study Clinician will review quarterly a cumulative summary of the AEs reported. The Study Clinician will review (in compliance with FHI SOP) all SAEs.

## **10.3 Data Monitoring Committee**

A Data Monitoring Committee (DMC) will review the safety profile of this study while the study is ongoing. The committee will convene 6 and 12 months after start of enrollment. The DMC will examine the safety results of the trial. The results broken out by the treatment groups will remain masked for the FHI personnel.

No formal stopping rules will be used by the DMC for safety outcomes. Rather, a clinical assessment will be made to determine if the nature, frequency, and severity of adverse effects associated with TDF warrant the early termination of the study in the best interests of the participants.

FHI has no a priori intent to consider early termination of the study based on effectiveness so that the extended safety data can be collected. Data on safe use in non-HIV infected people for at least one year is as important as the HIV outcome.

## **11.0 DATA MANAGEMENT PLAN SUMMARY**

A detailed data management plan will be written prior to study initiation. It will be modified if significant changes are required, in order to document how data were handled in the study. The following is a brief summary of the plan.

Study sites will capture clinical data on paper DCFs. After each patient visit, sites will enter data directly from the source documents into the eDCF using InForm software. Once the data have been entered and submitted, the information is encrypted and transmitted over the Internet to a PharmaLinkFHI database server. The server runs the pre-programmed validation checks against the new data and immediately returns any automated queries to the site. An audit trail of each change to the data is captured within the system.

FHI clinical monitors will perform the in-house clinical review of the participant data remotely for clinical consistency, outliers, AEs, and other abnormalities. Based on this review, manual queries are entered into InForm and are immediately available to sites for reply. All queries are automatically tracked in the database for auditing purposes using a full audit trail.

Throughout the study, the PharmaLinkFHI data manager will review the data on an aggregate level to identify potential areas requiring further clarification and look for data quality trends. This review supplements the remote page-by-page eDCF review carried out by the FHI monitor, and allow PharmaLinkFHI to identify potential data inconsistencies that only appear when one value is compared to the other values that have been collected during the study. Regular aggregate data review will allow PharmaLinkFHI to substantially decrease the time to providing the data set for analysis by proactively addressing many data issues that usually only appear at the end of a study when the summary data displays are reviewed.

PharmaLinkFHI will perform adverse event coding using MedDRA, which is a standard dictionary and concomitant medication using WHO. FHI will review and approve all coding prior to final data base closure.

## **12.0 PROTOCOL VIOLATIONS**

Emergency departures from protocol that eliminate an apparent immediate hazard to participants and are deemed crucial for the safety and well being of that participant may be instituted for that participant only – the Investigator will contact FHI as soon as possible. The Investigator will notify the IRB and FHI Project Leader in writing as soon as possible and document on the DCF reasons for deviation and ensuing events.

### **12.1 Protocol Violations**

- Omission or inadequate administration of informed consent
- Inclusion/exclusion errors, including legal age limit
- Treatment errors: no treatment or incorrect treatment (including dose or regimen, expired product), participant compliance problems
- Missing or incorrectly timed study procedures and assessments
- Forcing a participant to enter or remain in the study
- Participants who should have been discontinued from the study due to protocol criteria, but were not

## **13.0 STUDY DOCUMENTS**

### **13.1 Study Initiation**

The following documents will be in place and monitored by a Clinical Monitor at the study site before any potential participants are contacted.

- Investigator's Brochure

- FDA Form 1572
- Signed protocol and amendments
- Sample DCFs
- Financial disclosure forms for Investigator and Sub-Investigator
- Information given to participants
  - Consent forms
  - Other written information
  - Advertisements
- Financial records
- Signed agreements between involved parties
- IRB approval
- IRB composition
- Regulatory authority approval
- CV for Investigator, Sub-Investigator, and Site Coordinator
- Laboratory test normal values
- Lab accreditation and lab supervisor's CV
- Instructions for handling of investigational product and trial related materials
- Shipping records
- Decoding procedures for masked trials
- Site Visit Log

### **13.2 Study Conduct**

During the study the following documents will be in place and periodically monitored by a Clinical Monitor at the study site. Revision of documents will be made if relevant.

- Revisions to the Investigator's Brochure
- Revisions to the FDA form 1572
- Revision to the Financial Disclosure forms
- Revision to the protocol and amendments
- Revisions to the DCFs
- Revisions of information given to participants
  - Consent forms
  - Other written information
  - Advertisements
- IRB approvals
- IRB composition changes
- Regulatory authority approvals
- CV for Investigator, Sub-Investigator, and Site Coordinator
- Updates of laboratory test normal values
- Documentation of investigational product and trial related materials shipment
- Relevant communications other than site visits
- Signed consent forms
- Source documents

- Copies of completed DCFs
- Copies of documentation of DCF corrections
- Notification of Investigator to FHI of SAEs
- Notification of Investigator to local IRB and Regulatory Authorities
- Notification by FHI or Sponsor to Investigator of safety information
- Interim or annual reports to IRB, Regulatory Authorities, and FHI
- Participant screening log
- Participant ID code list
- Participant enrollment log
- Investigational products accountability documents
- Staff signature list
- Site Visit Log
- Progress Reports to FHI

### 13.3 Study Completion

After completion of the study, all of the documents in 13.1 and 13.2 should be in the file together with the following.

- Investigational products accountability documents
- Documentation of products destruction (if destroyed at site)
- Complete participant ID code list
- Final report by Investigator to IRB, Regulatory Authorities, and FHI

### 13.4 Site Record Retention and Access to Documents at the Site

The signed original informed consent documents for each participant, pink copies of DCFs, and originals of all study documentation (e.g. drug inventory forms, participant clinic records, original laboratory reports, staff journals, etc.) will be retained by the Investigator. **No records may be destroyed without written permission from FHI.**

The investigator may be subject to a field audit by FHI to validate the participation of study participants and to verify the data reported on the DCFs. This audit could occur while the study is in progress or several years after the study is completed. All of the participants' records and other study documentation must be filed and accessible on short notice (3-5 days) during the study and subsequent retention period.

## 14.0 QUALITY CONTROL AND QUALITY ASSURANCE

### 14.1 Quality Control of the OMT Sampling

Each time that a scheduled blood specimen is drawn from the participants for the safety parameters, an OraQuick HIV test will be performed on the serum. OraQuick can be conducted using whole blood or serum as well as OMT. We will compare the results of the blood specimen

with the OMT specimen at screening, 1, 3, 6, 9, and 12 months during follow-up. Discrepancies will be addressed by testing with ELISA and if discordant, Western blot.

